# Efficacy and tolerability of oral gastrodin for medication overuse headache (EASTERN): Study protocol for a multicenter randomized double-blind placebo-controlled trial

**DOI:** 10.3389/fneur.2022.1095298

**Published:** 2023-02-22

**Keywords:** medication overuse headache, gastrodin, randomized controlled trial, detoxification, prophylaxis

## Abstract

**Background:**

Prophylactic medication in clinical detoxification programs for the treatment of medication overuse headache is still debated. Gastrodin, a main bioactive constituent of *Rhizoma Gastrodiae*, has been applied clinically to treat primary headache for more than 30 years in China due to its potential analgesic and anti-migraine mechanisms. However, clinical evidence supporting its routing use in MOH is insufficient. The present study aims to investigate the efficacy and tolerability of oral gastrodin in medication overuse headache.

**Methods:**

A multicenter, randomized, double-blind, parallel, placebo-controlled trial will be performed. A target sample size of 186 patients who fulfill the International Classification of Headache Disorders 3rd version (ICHD-3) criteria for MOH will be recruited and screened during a baseline screening period of 28 days before being randomly assigned to either the gastrodin or placebo group at a ratio of 1:1. Enrolled patients will be assessed for each 4 weeks during the 12-weeks double-blind phase and followed up at week 24. The primary endpoint is mean change in monthly headache day frequency. Secondary endpoints will be the proportion of remitted MOH, change in headache pain intensity, headache impact test (HIT-6) score, 50% responder rate, treatment failure, monthly acute medication intake days, and Short Form 36-Item Health Survey (SF-36) score. Tolerability will be assessed by drop-out rates though safety monitoring during treatment.

**Discussion:**

The findings of the present study may help to provide new evidence on gastrodin as a prophylaxis treatment with both efficacy and high tolerability for the treatment of MOH.

**Clinical trail registration:**

Chinese Clinical Trail Registry (ChiCTR2200063719), Protocol Version 1.1, May, 09, 2022.

## Introduction

### Background and rationale

Medication overuse headache generally refers to monthly headache days of ≥15 per month resulting from acute “medication overuse” (MO) defined as the frequent consumption of acute pain medications above a certain threshold (e.g., 10 or 15 days per month depending on the medication type) for ≥3 months. Diagnostic criteria for MOH were introduced in the International Classification of Headache Disorders, 2nd edition (ICHD-2) (1) without a the requirement of the diagnosis of chronic migraine (CM; see Appendix for details on MOH and CM). In the third edition beta version (ICHD-3β), updated in 2013, concurrent CM and MOH are diagnosed if both criteria are met (2). These criteria remain the same in the ICHD-3 criteria.

The prevalence of MOH is still uncertain (3) and varies from 2% in a recent population-based study (4) to 60% in the Global Burden of Disease Study (5). Whether MOH is a cause or consequence of frequent acute medication intake has been debated for years (6, 7). Nonetheless, MO and MOH management are important in clinical care. MO is associated with an increased risk of chronic headache (8) and chronic migraine (9, 10).

Prognosis of MOH due to different type of chronic headache is probably variable. Although there is evidence that chronic tension-type headache (CTTH) and CM may have partly distinct pathophysiological mechanisms, clinical experience suggests that these two clinical entities may be at opposite poles of a single disease spectrum (11, 12). Of note, CM with MO represents a more severe subgroup of patients and can be difficult to treat (13). In a preplanned subgroup analysis that evaluated efficacy and safety of erenumab in patients with CM and MO, the medication overuse subgroup had a higher proportion of failing to respond to preventive treatment (14).

Effective education for people with MOH plays a major role in effective withdrawal therapy. Successful educational interventions rely largely on a productive doctor-patient alliance (15) and patients' motivation for adherence. In addition, it is often recommended to add a preventive therapy or optimize existing preventive regimens to reduce the number of monthly headache days, improve sense of self efficacy and as a result reduce both the physical and psychological need for acute medication for migraine. Preventive treatments may be pharmacologic, non-pharmacologic, or both.

Moreover, the addition of behavioral therapies to medication withdrawal has been shown to significantly improve outcomes and the maintenance of benefits when measured at 3 years post treatment) (16, 17). Results from a previous systematic review (18) and a newly published randomized clinical trial (19) support a program of prophylaxis treatment together with abrupt withdrawal of acute analgesic intake for treating MOH. Evidence from randomized controlled trials confirms complete withdrawal of the offending acute medication(s) is an effective treatment for MOH (20–22), but withdrawal symptoms may lead to treatment failure or rebound reactions. In the past two decades, it has been suggested that prednisone may be effective in reducing withdrawal symptoms (23, 24). However, results from a well-designed controlled trial confirmed no therapeutic effect of prednisolone on MOH (25). Therefore, an acceptable level of evidence in the recommending use of any of prophylactic medications or treatments other than behavioral therapies is still undetermined up to now (26). Hence the utility in bridging therapy using a preventive drug during the withdrawn phase needs to be determined. Topiramate is the first choice for people with MOH despite frequent adverse events (27). Data from our ongoing network meta-analysis (PROSPERO, CRD 42021193370) indicate that despite lower safety and greater tolerability issues, topiramate has large beneficial effects on reducing headache frequency and monthly acute medication intake frequency. Onabotulinumtoxin A and the humanized monoclonal calcitonin gene-related peptide (CGRP) antagonists eptinezumab and fremanezumab, are also helpful for reversion to no medication overuse; however, until CGRP antagonists are readily available around the world there are challenges with cost-effectiveness and accessibility.

*Rhizoma Gastrodiae*, a kind of traditional Chinese herb medicine, was firstly recorded for treating primary headache in a famous compendium of Chinese medicines called *Sheng Nong's Herbal Classic* in 25 AD to 220 AD. Gastrodin (4-[β-D-glucopyranosyloxy] benzyl alcohol) is the main bioactive constituent of *Rhizoma Gastrodiae* and has been applied clinically as an analgesic to treat migraine and other types of headache for more than 30 years in China (28). Several potential anti-migraine mechanisms of gastrodin have been discovered including inducing a dose-dependent reduction of CGRP- mRNA expression similar to flunarizine (29), preventing the release of CGRP from pre-synaptic central projections, inhibiting the post-synaptic effects of the ERK1/2 downstream signaling pathway to inhibit the firing of second-order trigeminal nociceptive neurons (30), altering acid-evoked membrane excitability of rat dorsal root ganglion neurons and decreasing the amplitude of the depolarization (31). Gastrodin has determined to be safe for use in toxicity studies in animals and occasionally reported adverse drug reactions (ADR) or events (ADE) in clinical practice (32). Recommended dosage of oral gastrodin for treating episodic migraine is 300 mg/day. Although there is no evidence that gastrodin is superior to other analgesics in treating primary headache, low quality evidence obtained from the tremendous amount of case series and observational studies indicates that gastrodin is beneficial for reducing headache frequency and headache intensity with increased dosage. This may largely be explained by the phenomenon that gastrodin is not brain penetrant with a cerebrospinal fluid /plasma ratio of only 5.5% (33). So theoretically, increasing the dosage of gastrodin maybe an ideal option for better efficacy. Previously, the safety of intravenous 40 mg/kg (up to 2,400 mg/day for a 60 kg human) gastrodin had been determined in a clinical trial (34). For efficacy and safety concern, the dosage of oral gastrodin in the present trial will be increased to 600 mg/day.

### Objectives

We will test the hypothesis that gastrodin may serve as a candidate therapy drug during the detoxification phase of MOH with advantages of improving chances of treatment adherence and success. The present study aims to determine the efficacy and tolerability of oral gastrodin as a prophylaxis treatment in MOH.

### Trial design

This is an investigator-initiated, multicenter, 1:1 ratio randomized, double-blind, parallel-group, placebo-controlled trial which consisted of a 28-day screening period, and a 12-week intervention period, with a final evaluation at week 24. A schematic diagram of study design is provided in Figure 1. The protocol of the present study has been registered in the Chinese Clinical Trial Registry (ChiCTR2200063719).

**Figure 1 F1:**
[figure not shown]
Schematic diagram of study design.

## Methods: Participants, interventions, and outcomes

### Study setting

Eligible patients will be screened at neurological outpatient clinic from three study sites at different provinces in China: Affiliated hospital of Yunnan University, Kunming, Yunnan; Xiangya Changde Hospital, Changde, Hunan; and Affiliated hospital of Chengdu University, Chengdu, Sichuan; and Puer People's Hospital, Puer, Yunnan. These sites are all tertiary hospitals which may provide extensive healthcare service for persons with headaches.

### Eligibility criteria

#### Inclusion criteria

Eligible patients are men or women aged 18–70 years with a pre-existing headache disorder onset at or before age 50, fulfilling the ICHD-3 diagnostic criteria for MOH (coded as 8.2) (35) with ≥15 headache days per month and with regular overuse of acute pain medications ≥ 10 or 15 days per month depending on the medication type for ≥ 3 months.

#### Exclusion criteria

Patients who previously received onabotulinum toxin A, nerve block anesthesia or transcranial magnetic stimulation during the 4 months before screening, who are unable to provide headache diary during the screening period, who have history of stroke, epilepsy or receiving antiepileptic drugs, and females who are breast feeding, pregnant or planning a pregnancy during the study will be excluded.

### Interventions

All patients will receive full individualized brief intervention (BI) education according to Kristoffersen et al.'s strategy (36) before randomization.

In the gastrodin group, patients will receive gastrodin 600 mg/day (200 mg tid) from baseline to the end of week 12. In the placebo group, matching placebo made of starch will also be prescribed three times a day. If a patient experience unacceptable adverse events as recorded in the instructions for gastrodin such as dry mouth, dizziness and upper abdominal discomfort, the target dose will be tapered down to 300 mg/day.

During the 24-week study period, their usual acute medication intake will be restricted to ≤ 2 days per week. Participants will be asked to return the experimental drug (or placebo) packaging at week 4, and week 8 in the clinic in order to get drugs for the next 4 weeks.

### Outcome measures

As there is a lack of guidelines for reporting results from clinical trials on MOH, we will adopt Hagen et al.'s suggestion on endpoints for MOH studies in follow-up including headache days/month, acute medication use days/month, headache intensity, cured MOH, and responder rate (37).

Primary efficacy endpoint is reduction in the mean number of monthly headache days from baseline at 24-week follow-up.

Secondary efficacy endpoints include:

a. Headache intensity at 12 and 24-week follow-up. The headache intensity at each headache onset will be measured on a 4-point scale (0 = pain, 1 = mild pain, 2 = moderate pain, 3 = severe pain), and be calculated as the average of headache intensity at each headache onset for 1 month;b. Proportion of cured MOH, defined as a patient does not fulfill the diagnostic criteria for MOH in ICHD-3 at 12 and 24-week follow-up;c. Mean change from baseline in total HIT-6 score and the proportion of patients with a ≥ 5-point reduction in total HIT-6 score (38) at 12 and 24-week follow-up. For total HIT-6 scores, a between-treatment group minimally important difference (MID) has been established as ≥2.3 (39). Additionally, a clinically meaningful change for an individual patient has been defined as a ≥ 5-point decrease in total HIT-6 score;d. 50% responder rate, defined as 50% reduction of from baseline in number of moderate or severe headache days at 12- and 24-week follow-up;e. Treatment failure, defined as use of acute medication intake >2 days per week during 12-week treatment;f. Reduction in the mean number of monthly medication intake days for treatment failures at 12- and 24-week follow-up;g. Quality of life (QoL), as measure by the Short Form 36-Item Health Survey (SF-36) (40) at 12- and 24-week follow-up.

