### Sample size

We will estimate each of the above mentioned variables to calculate endpoints for MOH studies according to a published study (22). Hypothesis test will be 2-tailed with 90% power and a significance level of *P* < 0.05. Sample size estimations for the four recommended endpoints are provided in Table 2.

**Table 2 T2:** Sample sizes estimation for each critical endpoint.

**Endpoints**	**Target power**	**Alpha**	**N1**	**N2**	**N**	**Assumed proportion (or mean) for treatment group**	**Referred proportion (or mean ±SD) for control group^*^**	**Difference between groups**
Reduction in monthly headache days	90%	0.05	77	77	154	46%	22%	24%
Cured medication overuse headache	90%	0.05	44	44	88	90%	62%	28%
Headache intensity	90%	0.05	22	22	44	20.7	38.4 ± 17.4	17.7

* Data referred for sample size estimation are all obtained from a published study (reference 16) which enrolled patients with medication overused headache who were assigned to restricted acute medication intake group (allowing to take up to 2 days a week with analgesics or migraine medication during the study period).

Finally, we assume group sample sizes of 77 in gastrodin group and 77 in the control group will achieve 90.188% power to detect a difference between the group proportions of 24%. The proportion in the gastrodin group is assumed to be 22% under the null hypothesis and 46% under the alternative hypothesis. The proportion in control group is 22% based on previously published literature (22). The test statistic used is the two-sided *Z*-Test with unpooled variance. To allow for 20% dropouts, we will include 186 patients, corresponding to 93 in each group.

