## Methods: Data collection, management, and analysis

### Data collection methods

Baseline survey and efficacy assessments will be based on information recorded by participants using an eDiary mobile application. Baseline information includes age, educational level (years), any medical history, family history of headache, body mass index, age of headache onset, pre-exiting headache type, monthly headache days, and month medication intake days.

Following variables will be recorded both at baseline survey and each headache attack after randomization: headache characteristics, headache associated symptoms, the headache pain intensity, pain duration of an attack (hours), and acute medication use (type and dosage).

Monthly headache days, month medication intake days, the headache pain intensity, score of HIT-6 and SF-36, treatment failure, drop-outs and any adverse events will be assessed at 4, 8, 12, and 24-week follow-up.

A summary table of eDiary is shown in Table 3. Training for the eDiary will be provided for qualified participants during before randomization.

**Table 3 T3:** Summary of data collection from eDiary.

**Variables recorded**	**Day-28–0**	**At each headache onset after randomization**			
Age	x				
Body mass index	x				
Education years	x				
Age of first headache onset	x				
Any medical history	x				
Family history of headache	x				
Diagnosis of pre-existing headache	x				
Monthly headache days	x				
Month medication intake days	x				
Headache pain characteristics	x	x	x	x	x
Headache associated symptoms	x	x	x	x	x
Headache intensity	x	x	x	x	x
Duration of headache pain (hours)	x	x	x	x	x
Type of acute pain medication intake	x	x	x	x	x
Dosage of acute pain medication intake	x	x	x	x	x

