### Statistical methods

All analyses on efficacy endpoints will be performed using the intention-to-treat (43) principle which includes all randomized patients who had an evaluable baseline period of eDiary data (week-0), received at least 1 dose of gastrodin or placebo, and had at least one evaluable follow-up appointment. Safety evaluations will be performed consisting of all participants who received at least 1 dose of study intervention.

Continuous variables are presented as mean ± standard deviation (44) conforming to the normal distribution and median (interquartile range; IQR) for the skew distribution data. Student's *t*-test and Mann-Whitney *U*-test will be used to test differences in continuous variables where appropriate. Categorical variables will be expressed by the number and percentage of occurrences. Differences between two groups will be compared using chi-squared tests or Fisher's exact test where appropriate.

Cox proportional hazard regression (backward stepwise method) analysis and the Kaplan-Meier survival curve will be performed when necessary.

To more completely understand the clinical meaningfulness of the new therapy for MOH results from different headache type, we will conduct a subgroup analysis based on prior headache type (CM/CTTH or CM/ other types of headaches) for all the efficacy endpoints.

Participants who do not complete or are lost to follow-up will be coded as treatment failure, missing values will be handled using multiple imputation method under the missing-at-random (MAR) assumption (45).

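### Headache intensity (secondary endpoint a) is averaged only over headaches that occur: a headache-free month has no value, fewer headaches need not lower the score, and Table 2 sizes a different measure

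*Protocol article*

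**What the plan says.** Under Outcome measures, the first secondary endpoint is "Headache intensity at 12 and 24-week follow-up". Intensity at each headache onset is "measured on a 4-point scale (0 = pain, 1 = mild pain, 2 = moderate pain, 3 = severe pain"; the label of the 0 level presumably should read no pain. The monthly value is then "calculated as the average of headache intensity at each headache onset for 1 month".

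Data collection methods lists intensity among the items for which "Following variables will be recorded both at baseline survey and each headache attack after randomization", and Table 3 has the same layout: after randomisation, intensity is entered at headache onset. No section scores a headache-free day or assigns a value to a month without headache.

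For absent data, Statistical methods codes participants who do not complete or are lost to follow-up as treatment failures, and adds that "missing values will be handled using multiple imputation method under the missing-at-random (MAR) assumption".

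Table 2 (Sample size) has a row for headache intensity: assumed mean 20.7 on treatment, 38.4 ± 17.4 on control, difference 17.7, 22 per group.

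**The concern.** The denominator is the number of headaches that occurred, and treatment is meant to change that number. Three problems follow.

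- The best possible outcome, a month without headache, gives no score. The 0 level of the scale does not help, because a rating exists only when a headache starts. Such a value is undefined and not merely unobserved, so imputing it under missing at random would be inappropriate.
- The between-group comparison is conditioned on the headaches left after randomisation. A treatment that lowers frequency can look neutral on this score and, under some patterns of effect, unfavourable.
- The figures used to size the endpoint cannot come from the endpoint as defined.

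At stake is the reading of a secondary endpoint that is reported at weeks 12 and 24 and is one of the three rows in Table 2.

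**Working it through.** **Table 2 first.** Inputs: difference 17.7, SD 17.4, two-sided alpha 0.05, power 90% (Sample size). Normal approximation: n = 2 × (1.960 + 1.282)² × (17.4/17.7)² ≈ 20.3, so 21 per group. With the noncentral t distribution, power is 0.895 at 21 and 0.909 at 22 per group, so 22 are needed. The stated 22 is reproduced, and these figures were therefore the ones used.

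An average of ratings from 0 to 3 lies between 0 and 3, and its SD cannot exceed half the range, 1.5. The values 38.4, 20.7, 17.7 and 17.4 all lie outside these limits. The article does not say which measure they describe. It gives no mean or SD on the 0-3 scale, so the row cannot be recalculated from the documents.

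**The averaging rule.** Let m, o and s be the numbers of mild, moderate and severe headaches in 28 days.

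- Monthly sum = m + 2o + 3s
- Onset average (as planned) = sum / (m + o + s)
- All-days mean = sum / 28, with headache-free days scored 0

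The counts below are assumptions for illustration, with one onset per headache day. Both starting patterns have 20 headache days, in line with entry "with ≥15 headache days per month".

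| Pattern (m/o/s) | Sum | Onset average | All-days mean |
|---|---|---|---|
| 10/5/5, start | 35 | 35/20 = 1.75 | 1.25 |
| 0/5/5, all mild removed | 25 | 25/10 = 2.50 | 0.89 |
| 8/8/4, start | 36 | 36/20 = 1.80 | 1.29 |
| 4/8/4, half of mild removed | 32 | 32/16 = 2.00 | 1.14 |
| 4/4/2, half of each removed | 18 | 18/10 = 1.80 | 0.64 |
| 8/12/0, severe become moderate | 32 | 32/20 = 1.60 | 1.14 |
| 0/0/0, no headache | 0 | 0/0, undefined | 0 |

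In the first pair the planned score rises by 43% (2.50/1.75 = 1.43) while the monthly sum falls by 29% (25/35 = 0.71). Halving every severity leaves the planned score unchanged. When attacks become milder without becoming fewer, it falls as it should.

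**How often there is no value.** If onsets follow a Poisson distribution with mean 20 per month (assumed), the chance of none is exp(−10) = 0.00005 after a 50% cut and exp(−2) = 0.135 after a 90% cut. Patients without a score would therefore range from practically none to about 13%, depending on the effect.

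**The case against.** Per-headache severity is a legitimate quantity in its own right. The article lists frequency and intensity separately: the primary endpoint counts headache days and endpoint d uses moderate or severe headache days, so a reader could see fewer headaches beside a higher average among those left. An unchanged average after a proportional cut is the right answer to the question of how bad the remaining headaches are. This stands, and it argues for adding a second score and against discarding the first.

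A reader might infer that gastrodin will appear harmful on intensity. The documents do not support that. The reversal needs an effect mainly on mild headaches in patients who keep moderate or severe ones. The Introduction expects lower frequency and lower intensity, and if attacks become milder the planned score falls.

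A reader might also infer that headache-free patients will be imputed. The article does not say so. Its sentence on missing values follows a clause about non-completers, and a fuller document could code such a month as 0. What stands is that no value is given for it here, and that the only stated rule for absent values would be the wrong one. Such months are also likely to be few unless the effect is large.

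It would likewise go too far to say that the comparison is no longer between randomised groups. Every patient with at least one headache contributes a value, which is nearly everyone unless the effect is very large.

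Finally, an all-days score is not free of difficulty. The diary is described as entered at headache onset, so a headache lasting several days may carry one rating, and an empty day may be headache-free or simply unrecorded. This stands and shapes the fix.

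**Conclusion.** The point holds as a defect in the definition of a secondary endpoint. Two parts need no assumption: the onset average is undefined for a headache-free month, and the Table 2 figures cannot be averages on a 0-3 scale, so the endpoint sized is not the endpoint defined. The insensitivity to a proportional fall in headaches follows from the formula. The change from 1.75 to 2.50 rests on assumed counts and an assumed effect on mild headaches only; it shows what the score can do and predicts nothing about this trial. The share of patients without a value (practically none to about 13%) rests on the assumed Poisson model.

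A reader might take the scale mismatch to undermine the total sample size. It does not: the trial is sized on the headache-day row at 77 per group, raised to 93 per group and 186 in all, and the intensity row asks for only 22 per group. The change is worth making before unblinding, but neither the primary analysis nor the recruitment target depends on it.

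**What to change.** - State that a month the diary confirms as headache-free is scored 0 for endpoint a and is not imputed. Keep unrecorded days distinct from headache-free days, so that diary lapses are not counted as the best outcome.
- Report beside the per-headache average a 28-day mean of daily worst intensity, with headache-free days scored 0. Read the per-headache average as a description of the remaining headaches.
- Re-base the Table 2 intensity row on the score actually defined, or delete the row if no mean and SD on that scale are available.
- Correct the label of the 0 level.

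The cost is mainly wording. Endpoint d already needs severity by day, so the all-days score asks for little beyond what the trial must derive anyway. It does need a stated rule for days on which an earlier headache continues and, if the eDiary has none, a way of confirming a headache-free day. The downside is that the all-days score combines frequency with intensity and so correlates with the primary endpoint, which is why both scores should be shown.

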## Discussion

Findings from the present study may help to provide an evidence-based choice for reducing acute medication overuse headache among patients with chronic headache. Data from observational studies, clinical, and animal studies *in vivo* had confirmed the anti-migraine or analgesic effect of gastrodin but lack of convincible evidence supported by controlled trials. Acute withdrawal of overused medications is recommended by guidelines together with oral or subcutaneous prophylactic medication (27). The present two-arm placebo-controlled trial will investigate the efficacy of gastrodin in reducing monthly medication intake days, monthly headache frequency and improving health outcomes for people with MOH. We will also anticipate a higher acceptability and tolerability of gastrodin due to lower occurrence of serious adverse events brought by oral gastrodin in previous reporting.

Treatment options for withdrawal symptoms in the acute phase of detoxification vary considerably between studies including fluid replacement, analgesics, tranquilizers, neuroleptics, amitriptyline, valproate, intravenous dihydroergotamine, oxygen, electrical stimulation (46), diclofenac or naproxen orally, and/or metoclopramide, and behavioral therapies (47). Considering patients' clinical compliance to withdrawal treatment, bridging therapy is need other than specific symptomatic drugs. This hypothesis had been confirmed by a recently published 3-arm controlled trial (19). However, the best choice for bridging therapy is still debated. To avoid treatment failure to the most extent, we will introduce BI education (36) to all participants before randomization. The efficacy of BI scheme for MOH had been confirmed by a double-blinded cluster randomized controlled trial and recommended by a newly updated guideline (27). Taken together, we will look forward to imparting advice with restricted medication intake combined with oral gastrodin as a bridging therapy that may beneficial for patients with MOH with significant curative effect and better compliance.

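### Secondary endpoint (f) compares acute-medication days only among treatment failures, a set formed after randomisation by the same variable, and contradicts the unrestricted endpoint stated elsewhere

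*Protocol article*

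**What the plan says.** In the protocol article, Outcome measures, endpoint (e) is "Treatment failure, defined as use of acute medication intake >2 days per week during 12-week treatment". Endpoint (f) follows: "Reduction in the mean number of monthly medication intake days for treatment failures at 12- and 24-week follow-up". The limit behind (e) applies to everyone. Under Interventions, for the whole 24 weeks, "their usual acute medication intake will be restricted to ≤ 2 days per week".

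Statistical methods enlarges the failure group: "Participants who do not complete or are lost to follow-up will be coded as treatment failure". The same section states: "All analyses on efficacy endpoints will be performed using the intention-to-treat (43) principle".

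Elsewhere medication days carry no restriction to failures:

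- The Abstract (Methods) lists "monthly acute medication intake days" among the secondary endpoints.
- The opening of Outcome measures adopts a published set of endpoints that includes days of acute medication use per month, with no subset named.
- The Discussion says the trial will "investigate the efficacy of gastrodin in reducing monthly medication intake days", among other aims, in people with MOH.
- Table 1 schedules medication intake days at baseline and at weeks 4, 8, 12 and 24, with no limit to failures.

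**The concern.** Patients enter the set analysed in (f) because of their medication use after randomisation, and (f) then compares medication use between arms within that set. If gastrodin lowers intake, some patients who would have failed on placebo stay under the limit on gastrodin and leave the set. Those who remain in the gastrodin arm are, on average, the heavier users. The two groups of failures are then no longer comparable by randomisation, and the difference between them mixes the drug's effect with this selection. A difference in dropout between arms would alter the set in the same way, because dropouts are coded as failures.

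Medication use is the behaviour that defines MOH. As the detailed list stands, the only comparison of it across all patients is the yes/no endpoint (e). The number of days, which uses more of the information collected, is compared only in the selected set. A drug that works could look weaker on (f) than it is, and the comparison would use fewer patients.

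**Working it through.** The protocol states no figure for (f), for the failure rate or for medication days, so there is no figure of its own to reproduce. All distributions below are assumptions. From the document come the limit of 2 days per week (2 × 4 = 8 days per 4 weeks), 1:1 allocation, and 77 evaluable patients per arm (Sample size). The illustrations leave out dropouts coded as failures.

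**1. Follow-up level, failure read as more than 8 days per 4 weeks.** Assume Normal with SD 4 and mean 9 on placebo, 7.5 on gastrodin. With a = (8 − μ)/σ, the failure proportion is 1 − Φ(a), and the mean among failures is μ + σφ(a)/(1 − Φ(a)).

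- Placebo: a = −0.25; failures 60%; mean among them 9 + 4 × 0.387/0.599 = 11.58.
- Gastrodin: a = 0.125; failures 45%; mean among them 7.5 + 4 × 0.396/0.450 = 11.02.
- Difference among failures: 11.02 − 11.58 = −0.56 days. In all patients it is 7.5 − 9 = −1.5, or −1.47 by simulation with values held within 0 to 28.

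**2. Same inputs, failure read as any one of 12 weeks above 2 days** (weekly counts assumed binomial). Failures are 88% vs 80%. The difference among failures is −1.02, against about −1.45 in all patients. The estimate is still attenuated, but less.

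**3. Change from baseline, which is what (f) measures.** Assume baseline about 20 days (SD 5), follow-up SD 6, and failure above 8 days per 4 weeks at the analysed time point. The table shows a true effect of 3 days with 77 per arm. Differences are in mean reduction; positive favours gastrodin.

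| Placebo follow-up mean; correlation with baseline | Failures, placebo vs gastrodin | Difference, all patients | Difference, failures only | Power, all vs failures only |
|---|---|---|---|---|
| 8; 0.3 | 50% vs 31% | 2.58 | 1.40 | 77% vs 18% |
| 10; 0.5 | 63% vs 43% | 2.76 | 1.85 | about 90% vs 43% |
| 12; 0.7 | 75% vs 57% | 2.87 | 2.27 | 99% vs 83% |

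For true effects of 2 to 4 days, the failures-only difference was about 53% to 80% of the all-patient difference. In the middle row the subset holds about 49 placebo and 33 gastrodin patients. Mean baseline use among them is 21.3 vs 22.0 days, so the arms already differ at baseline. With no effect in any patient, both differences are 0.

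**4. Can the sign reverse?** Take four patients with untreated follow-up of 4, 9, 10 and 16 days, all with baseline 20, and a drug that lowers each by 3 days.

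- All patients: mean reduction 20 − 9.75 = 10.25 on placebo and 20 − 6.75 = 13.25 on gastrodin, a benefit of 3.0.
- Failures on placebo (9, 10, 16): (11 + 10 + 4)/3 = 8.33. The only failure on gastrodin (13): 7.00. The apparent result is 1.33 days worse.

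This depends on the common baseline. Take equal numbers of milder failures (10 days) and heavy ones (16 days), with the drug removing half of the milder failures and none of the heavy ones. Mean reductions among failures, with weights 1:1 on placebo and 0.5:1 on gastrodin, are:

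- Baselines 20 and 20: (10 + 4)/2 = 7.0 vs (0.5 × 10 + 4)/1.5 = 6.0. Reversed.
- Baselines 18 and 24: both types reduce by 8, so 8.0 vs 8.0. No difference.
- Baselines 16 and 24: (6 + 8)/2 = 7.0 vs (0.5 × 6 + 8)/1.5 = 7.33. Favours the drug.

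**The case against.** The strongest defence is that the protocol plainly intends an all-patient comparison. The Abstract, the opening of Outcome measures and the Discussion name medication days without a subset, Table 1 schedules them at every assessment, and efficacy analyses are placed under intention-to-treat. Endpoint (e) already compares medication use across arms as a yes/no outcome. A reader might infer from (f) that the effect on medication use in all patients is never tested. The documents do not support that. What stands is narrower: the detailed list has no all-patient comparison of medication days, and this contradicts the other sections.

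Two further objections limit the size. The amount of distortion depends on how failure is read, because the wording of (e) could mean a monthly total or any single week. And (f) is a change from baseline, so illustrations using follow-up levels alone are only a guide. Both points are right, but attenuation remained under both readings of failure and in the simulation of change from baseline.

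A reader might also infer that dropouts enter the subset with no medication data at all. That goes too far. The efficacy set requires at least one evaluable follow-up appointment, and missing values are to be multiply imputed. Dropouts may lack week-12 or week-24 data, and their values there would then be imputed.

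**Conclusion.** The point holds. Endpoint (f), followed as written, is not a randomised comparison if gastrodin affects medication use or dropout, and it conflicts with the protocol's own intention-to-treat statement and with its unrestricted descriptions of the endpoint. Under the assumed distributions the usual consequence is attenuation: from about −1.5 to −0.56 days under the monthly reading, from about −1.45 to −1.02 under the any-week reading, and to about 53% to 80% of the all-patient difference when change from baseline is simulated.

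Two stronger readings are not supported. The comparison is not biased in every case: with no effect on medication use or dropout in any patient, it is unbiased. Nor is reversal the expected result: it appeared only in constructed examples with similar baselines in milder and heavier users, and not in the simulation for effects of 2 to 4 days.

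This should be fixed. It is one secondary endpoint, and the primary endpoint and the sample size are unaffected.

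**What to change.** In Outcome measures, remove the restriction to treatment failures from (f). Define it as change from baseline in monthly acute-medication days at weeks 12 and 24 in all randomised patients, analysed under the plan's intention-to-treat and imputation rules. Make the Abstract and the detailed list agree. If a summary among failures is wanted, present it by arm as descriptive, with no between-group test. Endpoint (e) can stay as the yes/no comparison.

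The cost is a short wording change, best made before unblinding. Table 1 already schedules the measure at every assessment with no limit to failures, so neither data collection nor sample size changes.
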